## Abstract

**Background:**

Previous studies show that insomnia and hypertension are closely related. Currently, intervention for hypertension with insomnia has become a research hotspot. Acupuncture, as a representative non-pharmaceutical therapy of traditional Chinese medicine (TCM), has been widely used in improving insomnia and hypertension. However, there are few clinical studies on acupuncture for hypertension with insomnia.

**Methods:**

A single-center, subject-and-assessor-blind, randomized, sham-controlled trial has been designed for a study to be conducted in Jiangsu Province Hospital of Chinese Medicine. Sixty eligible patients will be randomly assigned to the treatment group and the control group in a 1:1 ratio. The treatment group will receive acupuncture treatment, while the control group will receive sham acupuncture treatment. Both groups will be treated three times per week for 4 weeks. Data will be collected at baseline and after 4 weeks of treatment and analyzed by using SPSS 25.0. The primary outcome measures are sleep parameters of portable polysomnography before and after treatment. Secondary outcomes are Pittsburgh Sleep Quality Index, Insomnia Severity Index, home blood pressure, and heart rate variability.

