Sympathetic nervous system hyperactivity is often considered to be one of the mechanisms for the comorbidity of insomnia and hypertension (26, 27). The hyperarousal hypothesis holds that chronic insomnia is a manifestation of physiological hyperarousal, during which insomnia patients have a persistent increase in sympathetic excitation. And sympathetic nerve overexcitation will constrict blood vessels and increase blood flow resistance, thereby increasing blood pressure and increasing the risk of hypertension (28). Moreover, the autonomic nervous system is involved in the regulation of the circadian rhythm of blood pressure, and rhythm disorders of the autonomic nervous system can cause blood pressure rhythm disturbance, resulting in non-dipper or even anti-dipper blood pressure rhythms (29, 30). Heart rate variability (HRV) is a non-invasive quantitative indicator that can effectively monitor autonomic nerve regulation in clinical practice, and can reflect individual sympathetic and parasympathetic nervous function states (31, 32). Therefore, the change of heart rate variability is the underlying mechanism of acupuncture intervention on the comorbidity of hypertension and insomnia.

Based on the above, we design a randomized, sham-controlled trial that the main purpose is to explore the effects of acupuncture on objective sleep and blood pressure of hypertensive patients with insomnia by using PPSG combined with sleep scales and the secondary objective is to investigate the mechanism of acupuncture treatment in the comorbidity of hypertension and insomnia by HRV data collected by single-lead portable electrocardiograph (ECG).

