### Outcome measures

#### Primary outcome measures

PPSG is one of the sleep monitoring methods with the advantages of supporting home environment monitoring and avoiding the influence of the first night effect, which can be used for objective diagnosis of insomnia, treatment evaluation and differential diagnosis of sleep diseases. In this study, Anbaolan wearable portable sleep recorder [202070644; Embla (Beijing) Medical Equipment Co., Ltd., Beijing, China] was applied to sleep monitoring. The device records electroencephalogram (EEG), electrooculogram (EOG) and electromyogram (EMG) signals through a set of head-mounted sensors, monitors blood oxygen with finger pulse oxygen, and uses AI intelligent algorithms to evaluate sleep structure in detail, including wakefulness (W) and rapid eye movement sleep (REM) sleep period), N1 stage sleep, N2 stage sleep, N3 stage sleep, and then the sleep quality evaluation indicators such as sleep efficiency (SE), sleep awakening times (SA) and total sleep time (TST) can be obtained, which can provide real-time and objective sleep evaluation indices for individuals. Sleep parameters of PPSG will be collected one night and evaluated before treatment and after 4 weeks of treatment.

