### Sample size

The calculation of sample size will be based on the change of ISI scores. According to the results of existing published literature (36), the overall standard deviation of ISI scores in patients of hypertension with insomnia was 5.5, ISI scores decreased by 3.3 after treatment, α = 0.05, β = 0.10, and *N* ≈ 24 cases were calculated. Considering the factors of contamination, non-compliance and shedding during the test, the shedding rate was determined to be 20%, so there were 30 cases in the treatment group and 30 cases in the control group. For comprehensive consideration, a total of 60 samples will be required for this study.

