### Statistical analysis

In this study, all statistical analyses will be conducted by an independent statistician using SPSS 25.0 software (IBM, Armonk, NY, USA). The measured data will be expressed as mean ± standard deviation, and the count data will be expressed by the ratio or composition ratio. For comparing measured data between the two groups, first normal analysis will be performed. A *t*-test will be used for the measured data conforming to normal and homogeneity of variance, and a nonparametric rank sum test will be used for non-normally distributed measured data. The data will be counted by the Chi-Square test or Fisher's exact test. *P* values ≤ 0.05 will be considered statistically significant.

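### The primary outcome is an open set of portable-polysomnography parameters, and none of them is named as the primary variable

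*Protocol article*

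**What the plan says.** The protocol article defines the primary outcome twice. The abstract (Methods) says: "The primary outcome measures are sleep parameters of portable polysomnography before and after treatment". The section Primary outcome measures describes a recorder whose algorithm evaluates sleep structure, "including wakefulness (W) and rapid eye movement sleep (REM) sleep period), N1 stage sleep, N2 stage sleep, N3 stage sleep", and then says that "the sleep quality evaluation indicators such as sleep efficiency (SE), sleep awakening times (SA) and total sleep time (TST) can be obtained". On timing it adds: "Sleep parameters of PPSG will be collected one night and evaluated before treatment and after 4 weeks of treatment".

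The section Statistical analysis gives one threshold for all comparisons: P "values ≤ 0.05 will be considered statistically significant". A t-test "will be used for the measured data conforming to normal and homogeneity of variance", and a rank sum test is used for non-normal data. No sentence says which sleep parameter carries the primary test, or how many must be significant.

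The section Sample size does not settle the matter either: "The calculation of sample size will be based on the change of ISI scores". The abstract lists ISI as secondary.

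**The concern.** Choosing the primary variable is core protocol content. It fixes in advance the result on which the trial will be judged. Here the article does address the choice, in two places, but each time gives a class of measurements instead of a variable. Because the indices are introduced as examples, even the number of candidates is open.

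Two things are at stake. First, with several candidates and one unadjusted threshold, the false-positive risk for a primary claim exceeds 5% if the claim may rest on whichever parameter turns out significant. Second, the parameters can disagree. Total sleep time might improve while awakenings do not, or the sleep stages might shift in opposite directions, and the article gives no predefined reading of such a pattern. This matters because the abstract says that a positive trial would supply strong evidence for acupuncture. An unnamed primary variable cannot support a claim of that strength.

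**Working it through.** **1. Does any part of the article single out one parameter?**

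- Abstract, Methods: PPSG parameters in the plural, none named.
- Primary outcome measures: five structure measures (W, REM, N1, N2, N3) and three indices (SE, SA, TST). That makes 3 named indices, or 5 + 3 = 8 named measures, in an open list.
- Sample size: inputs are an ISI standard deviation of 5.5, a decrease of 3.3, α = 0.05 and β = 0.10. The stated N ≈ 24 is reproduced by the one-sample, one-sided formula (5.5 × (1.645 + 1.282) / 3.3)² = 23.8, rounded up to 24; then 24 / 0.8 = 30. The suitability of that formula for a two-group trial is a separate matter. For this point, the calculation contains no PPSG quantity.

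The answer is no.

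**2. False-positive chance if any one significant parameter counted as success**

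This success rule is an assumption. For k independent tests at 0.05 with no true effect, the chance of at least one P ≤ 0.05 is 1 − 0.95^k:

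- k = 3: 1 − 0.95³ = 14.3%
- k = 8: 1 − 0.95⁸ = 33.7%

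The article gives no correlations, so a common correlation ρ between normal test statistics was assumed and simulated (400,000 draws per cell, two-sided tests):

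| ρ | 3 indices | 8 measures |
|---|---|---|
| 0 (exact) | 14.3% | 33.7% |
| 0.3 | 13.7% | 29.9% |
| 0.5 | 12.6% | 25.1% |
| 0.7 | 10.9% | 19.0% |
| 0.8 | 9.7% | 15.8% |
| 0.9 | 8.3% | 12.0% |
| 0.95 | 7.3% | 9.4% |

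Every cell exceeds 5%. Under any dependence at all, the Bonferroni bounds are 3 × 0.05 = 15% and 8 × 0.05 = 40%.

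**3. Counting only false positives that favour acupuncture**

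The nominal rate is then 2.5%. Independent tests give 1 − 0.975³ = 7.3% and 1 − 0.975⁸ = 18.3%. At ρ = 0.95 the simulated figures are 3.7% and 4.7%. For the sleep stages, the favourable direction would itself have to be defined.

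**4. What the remedies do**

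- One named primary parameter: error 5%.
- Bonferroni over three indices: each tested at 0.05 / 3 = 0.0167; family-wise error 1 − (1 − 0.0167)³ = 4.9% if independent.
- Bonferroni over eight: each tested at 0.05 / 8 = 0.00625; family-wise error 4.9% if independent.

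The power cost can only be illustrated, because no PPSG effect is given. Borrowing the ISI standardised effect 3.3 / 5.5 = 0.6 with 30 per arm, two-sided power is Φ(0.6 × √15 − z). This is 64% at 0.05 (z = 1.960), 47% at 0.0167 (z = 2.394) and 34% at 0.00625 (z = 2.734).

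**The case against.** Four objections deserve weight.

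**The stages may not be endpoints.** The five structure measures appear in a description of what the device does. The article does not say that each will be tested as a primary outcome. This stands: three named indices in an open list is the firmer reading, and eight is only a possibility.

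**Independence is not realistic.** Total sleep time is the sum of the sleep stages, sleep efficiency relates it to time in bed, and wakefulness is close to its complement. If two of the three indices were nearly collinear, there would be about two effective tests: 1 − 0.95² = 9.8%. This also stands. The independent-test figures are upper-end values.

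**The success rule is not written down.** A reader might infer that the plan lets the trial declare success on any one of eight tests, and so that its error rate is 34% and far above 5%. The article does not support that. It gives a significance threshold and no rule for success, and it does not give the number of tests or their correlation.

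**A statistical analysis plan may exist.** A multiplicity method can properly sit there, so the absence of an adjustment is not itself the fault. Such a plan would still inherit a protocol that names no primary variable.

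A reader might also count blood pressure as a further primary target, because the Introduction says that "the main purpose is to explore the effects of acupuncture on objective sleep and blood pressure of hypertensive patients with insomnia". That sentence states a purpose, while the outcome list places blood pressure among the secondary measures. It adds nothing to the error calculation. Nor does the exploratory wording of that sentence excuse the gap, given the strength of evidence that the abstract promises.

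**Conclusion.** The point holds as a defect in defining the primary variable. Nothing in the article designates one parameter, and the sample size does not reveal one.

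The size of the consequence is conditional. If one significant parameter were enough for a primary claim, the chance of at least one false positive would be about 7% to 14% for the three named indices and about 9% to 34% for all eight measures. This rests on three assumptions: the success rule, the number of parameters tested, and a common correlation between 0 and 0.95. The excess over 5% appears in every case computed. It is modest when the measures are strongly correlated and large only when many weakly correlated measures are tested.

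**What to change.** Before unblinding, name one PPSG parameter at week 4 as the sole primary outcome, compared between groups two-sided at 0.05. The choice is the sponsor's, on clinical grounds; sleep efficiency is one example. If several indices must stay primary, list them exhaustively and control the family-wise error across them, for instance with Holm's procedure. Classify the remaining PPSG parameters as secondary or descriptive, with confidence intervals.

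Trial status says that randomization began on 1 June 2022, so this changes the primary outcome of a running trial. It should be a dated amendment that records that the choice was made blind to group results. The amendment should also say that the ISI-based sample size gives no stated power for the chosen PPSG primary.

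The cost is a documented change of text, with no change to visits, measurements or treatment. The trial gives up the option of claiming primary success on another parameter. Keeping several primaries instead would cost power, as the illustration above shows.

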**Discussion:**

This study aims to evaluate the efficacy of acupuncture using the portable polysomnography combined with sleep scales, and analyze heart rate variability to preliminarily explore the underlying mechanism of acupuncture on hypertension with insomnia. The trail, if proven to be effective, will provide strong scientific evidence to support acupuncture is effective to manage patients for hypertension with insomnia.

**Clinical trial registration:**

ChiCTR2200059161.

## Introduction

Insomnia is one of the most prevalently encountered sleep disorder characterized by perceived difficulty in falling asleep and/or maintaining sleep, leading to unsatisfactory sleep (1). It has been reported that the prevalence of insomnia disorder in the general population has reached 10%−15% in China (2). Particularly, under the influence of factors such as the epidemic of coronavirus disease 2019 (COVID-19), the incidence rate is still ascending (3). Insomnia not only seriously harms patients' physical and mental health, but also increases the social medical burden (4). Studies have shown that insomnia can increase the risk of depression, dementia, hypertension, diabetes, tumors and other diseases (5–8). In particular, the relationship between insomnia and hypertension has attracted more and more attention from researchers over the last few decades. Hypertension, the most common chronic disease, is the main cause of death in patients with cardiovascular and cerebrovascular diseases. In China, 2.33 million people die from cardiovascular and cerebrovascular diseases caused by hypertension every year (9). The awareness rate, treatment rate and control rate of hypertension were 46.9, 40.7, and 15.3%, respectively, which are far lower than developed countries (10). Therefore, it is crucial to seek a positive and stable antihypertensive strategy for preventing cardiovascular and cerebrovascular diseases in China.

There are many factors influencing hypertension (11), such as smoking, diabetes, dyslipidemia, obesity, and unhealthy diet. Currently, it is clinically found that insomnia disorder is a common complaint of patients with hypertension, and insomnia and hypertension often co-exist. The findings (12) have suggested that the proportion of insomnia in hypertensive patients is 19%−47.9% compared with normal blood pressure, and the incidence of hypertension in insomnia patients is 21.4%−50.2% compared with normal sleepers. Numerous meta-analyses (7, 13, 14) have reported that insomnia is an important risk factor for hypertension. Jarrin et al. (13) summarized the potential mechanisms related to insomnia and hypertension, suggesting that insomnia may cause persistent hypertension through (but are not limited to) the activation of the autonomic nervous system (e.g., hyperactive sympathetic, lower parasympathetic), the renin-angiotensin-aldosterone system, the hypothalamic-pituitary-adrenal axis, and the immune system. In the past, due to the lack of public awareness of the relationship between insomnia and hypertension, most patients with hypertension and insomnia did not receive formal and active insomnia intervention in clinical practice, which is one of the reasons that blood pressure in patients with hypertension is difficult to control. At present, as the relationship between insomnia and high blood pressure is increasingly becoming a new focus of attention, many reports (15–17) have manifested that the combination with insomnia intervention on the basis of blood pressure reduction can contribute to controlling blood pressure and correcting blood pressure rhythm while ameliorating insomnia symptoms. However, benzodiazepines, the most commonly used in clinical treatment of insomnia, exist well-known side effects such as next-day hangover and drug dependence, which are not easily accepted by patients (18). The guideline-recommended cognitive behavioral therapy for insomnia (CBT-I) is difficult to implement clinically owing to its professionalism, long time-consuming, and poor patient compliance (19). Hence, it is critical to find safe and effective non-pharmaceutical therapy to further optimize the treatment mode of hypertension complicated by insomnia.

Acupuncture, as the most representative non-pharmaceutical therapy of TCM, has been widely applied to treat a variety of diseases ascribe to its unique advantages such as simplicity, safety, and no side effects. Now, acupuncture treatment of insomnia has been recommended by the “*Guidelines for the Diagnosis and Treatment of Insomnia in China*” (2). The meta-analysis (20) has revealed that acupuncture is effective in insomnia, and it is not a placebo effect. A small number of domestic studies have shown that acupuncture can improve the sleep quality of patients with hypertensive stroke, and the improvement of sleep quality can assist in regulating the early morning blood pressure of patients (21, 22). However, there are completely few clinical studies on the intervention of acupuncture on hypertension with insomnia, and it is still inconclusive whether acupuncture can improve insomnia and regulate blood pressure at the same time. In addition, the current researches have problems such as sleep outcome indicators mainly relying on scales and lack of objective evaluation. However, polysomnography (PSG), a “gold standard” assessment tool for the diagnosis of sleep disorders, is cumbersome to operate due to its large size and multiple leads, which not only affects the natural sleep state and fails to describe the real sleep state, but also lacks long-term monitoring conditions, causing it inconvenient for clinical practice (23). Compared with PSG, portable polysomnography (PPSG) has the superiorities of simple operation and home monitoring, small first-night effect, strong endurance and so on. Artificial Intelligence (AI) algorithm was used to evaluate sleep structure and sleep quality in detail, analyze and mark manual/automatic sleep-related events, judge and count micro-awakenings, and quickly identify sleep characteristic waveform, with an accuracy of 95% (24). The validity of PPSG in assessing Sleep has been recognized in several researches and meets the standards of America Academy of Sleep Medicine (AASM) (25).

Sympathetic nervous system hyperactivity is often considered to be one of the mechanisms for the comorbidity of insomnia and hypertension (26, 27). The hyperarousal hypothesis holds that chronic insomnia is a manifestation of physiological hyperarousal, during which insomnia patients have a persistent increase in sympathetic excitation. And sympathetic nerve overexcitation will constrict blood vessels and increase blood flow resistance, thereby increasing blood pressure and increasing the risk of hypertension (28). Moreover, the autonomic nervous system is involved in the regulation of the circadian rhythm of blood pressure, and rhythm disorders of the autonomic nervous system can cause blood pressure rhythm disturbance, resulting in non-dipper or even anti-dipper blood pressure rhythms (29, 30). Heart rate variability (HRV) is a non-invasive quantitative indicator that can effectively monitor autonomic nerve regulation in clinical practice, and can reflect individual sympathetic and parasympathetic nervous function states (31, 32). Therefore, the change of heart rate variability is the underlying mechanism of acupuncture intervention on the comorbidity of hypertension and insomnia.

Based on the above, we design a randomized, sham-controlled trial that the main purpose is to explore the effects of acupuncture on objective sleep and blood pressure of hypertensive patients with insomnia by using PPSG combined with sleep scales and the secondary objective is to investigate the mechanism of acupuncture treatment in the comorbidity of hypertension and insomnia by HRV data collected by single-lead portable electrocardiograph (ECG).

## Methods/design

### Design

A single-center, subject-and-assessor-blind, randomized, sham-controlled trial will be performed at Jiangsu Province Hospital of Chinese Medicine (Nanjing, China). A total of 60 participants will be randomly assigned to the treatment group (acupuncture group) and the control group (sham acupuncture group) in a 1:1 allocation ratio. Both groups will be treated three times per week for 4 weeks (12 sessions totally). The clinical trial conforms to Standard Protocol Items: Recommendations for Interventional Trials (SPIRIT) 2013 statement (33) as well as the Standards for Reporting Interventions in Controlled Trials of Acupuncture (STRICTA) (34). The study procedure and details are summarized in Figure 1 and Table 1.

**Figure 1 F1:**
[figure not shown]
Flow diagram of the trial.

**Table 1 T1:** Schedule of enrolment, interventions, and assessments.

**Time point**	**Study period**			
	**Baseline**	**Intervention**		**Post-** **treatment**
	−**1 week**	**Week 0**	**Week 4**	
**Enrolment**				
Eligibility screen	•			
Informed consent	•			
Medical history	•			
Physical examination	•			•
Random allocation	•			•
**Intervention**				
Acupuncture group (*n* = 30)		12 sessions of acupuncture in acupoints		
Sham acupuncture group (*n* = 30)		12 sessions of acupuncture with slight skin penetration		
Assessments				•
PSQI	•			•
ISI	•			•
HAMA	•			
HAMD	•			
Sleep-blood pressure diary	•	•	•	•
PPSG	•			•
Single-lead portable ECG	•			•
**Others**				
Success of blinding				•
Adverse events check		•	•	

PSQI, Pittsburgh Sleep Quality Index; ISI, Insomnia Severity Index; HAMA, Hamilton Anxiety Scale; HAMD, Hamilton Depression Rating Scale; PPSG, portable polysomnography; ECG, electrocardiograph.

### Patients

#### Recruitment strategies

This study will recruit patients of hypertension with insomnia through three approaches: (1) Regularly visit the Acupuncture and Moxibustion Rehabilitation Department, Physical Examination Center, and Hypertension Research Institute of Jiangsu Provincial Hospital of Traditional Chinese Medicine to collect cases; (2) Regularly distribute brochures in the halls of Jiangsu Provincial Hospital of Chinese Medicine or advertise on the screen to recruit qualified subjects; (3) Adopt WeChat platform to push articles to all the masses for recruitment.

